**3.2 - Sample size calculations.**

To be clinically reliable, the combined selective criteria must satisfy two requirements. First, intracranial injuries requiring neurosurgical intervention must never occur in blunt head trauma victims identified as risk free by the instrument. This is equivalent to requiring a 100% negative predictive value. Second, every blunt trauma victim with a significant intracranial injury must exhibit at least one of the risk criteria. This requirement implies that the sensitivity of decision instrument be 100%.

Verifying negative predictive value and sensitivity at an absolute level is not statistically possible with a finite sample size. However, it is possible to estimate limits for the true values of these proportions using exact statistical relationships. The lower confidence limit of a proportion (such as negative predictive value or sensitivity) is related to the total size of the study population. The quantitative relationship is expressed by the following equation [48]:

[figure not shown]

Where:

P_L_ = Lower confidence limit for the proportion being studied (i.e. the lower confidence limit for the negative predictive value or sensitivity of selective criteria).

X = Number of times the event of interest is observed.

N = Total number of observations.

α = Statistical confidence value (Set to 0.05).

ν_1_ = Degrees of freedom for the numerator; ν_1_ = 2 [ N - X + 1 ]

ν_2_ = Degrees of freedom for the denominator; ν_2_ = 2 X

F_α/2,ν1,ν2_ = One tailed value of the F-distribution with ν_1_ and ν_2_ degrees of freedom.

Validating a given P_L_ to a 95% level of statistical certainty implies that α = 5% (or α = 0.05). The main hypothesis of this study states that selective criteria will detect all intracranial injuries requiring neurosurgical intervention in blunt head trauma victims without missing any such injuries. Thus, for purposes of sample size calculations, for either negative predictive value or sensitivity, the event of interest (presence of one of the risk criteria) should occur with every observation. Hence, X = N.

The degrees of freedom for the numerator and denominator are then given by:

ν_1_ = Degrees of freedom for the numerator; ν_1_ = 2 [ N - X + 1 ] = 2 [ N - N + 1 ] = 2

ν_2_ = Degrees of freedom for the denominator; ν_2_ = 2 X = 2 N

The expression for the lower confidence limit then becomes:

[figure not shown]

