The research assistants will contact each patient at the time previously scheduled for their follow-up survey. If the patient is unavailable at the scheduled time, the assistants will attempt to re-contact the patient using the following schedule: two times on the day of the interview, once daily for five days after the date of the interview, and once weekly for three weeks after the date of the interview. Upon successful contact the assistants will either complete the survey or reschedule the interview depending on the patient’s preference. Contact will be abandoned, and the patient deleted from the work-up bias evaluation if the assistants are not able to contact the patient within four weeks of the scheduled survey date.

Once contact is established, the research assistants will administer the survey using the script presented in Appendix - D. Patients, or the care-takers of incapacitated patients, will be asked whether they sought care at another facility after their discharge, whether they received any x-rays or imaging studies, and if so, what type, and whether they received any treatments, hospital admission or brain surgery as a result of the injury. Patients will be considered to have had a significant intracranial injury if they had a neurosurgical procedure performed as a result of their injury. After the completion of each survey, the survey responses will be paired with matching criteria assessments to form a complete data record for each patient.

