TP_I_ = Number of imaged individuals requiring neurosurgery and labeled positive by the decision instrument (number of true-positives among imaged patients).

FN_I_ = Number of imaged individuals requiring neurosurgery and labeled negative by the decision instrument (number of false-negatives among imaged patients).

TP_W_ = Number of un-imaged individuals requiring neurosurgery and labeled positive by the decision instrument (number of true-positives among un-imaged patients).

FN_W_ = Number of un-imaged individuals requiring neurosurgery and labeled negative by the decision instrument (number of false-negatives among un-imaged).

Confidence limits for this measure will be calculated by applying boot-strap estimation to the entire UCLA cohort (both imaged and un-imaged patients) [73]. Estimates of the work-up bias associated with negative predictive value and specificity will similarly be calculated by computing the absolute difference of these values among imaged patients and the entire cohort.

These methods are similar to those used in assessing the potential for work-up bias in our previous derivation study (PHS Grant No. R01 HS08239). The methodology has shown to be reliable, and we were able to obtain follow-up survey information on 98% of the patients who agreed to participate in the study.

To verify the potential for work-up bias to with 1.0% requires a population of 368 head injury patients who do not receive CT imaging during their initial presentation. Thus we will enroll 368 consecutive patients in the work-up bias portion of the study.

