Errors in sensitivity and negative predictive value may also occur through biased enrollment. Practical concerns, such as cognitive impairment among head injury victims, make it impossible to obtain informed consent on all patients. To eliminate the potential for selection bias we instituted methodologies that allow us to conduct an observational study under a waiver of informed consent. This approach ensures that we will enroll all patients who undergo tomographic scanning (including those most likely to have intracranial injuries), but limits our ability to obtain CT scans on all blunt head injury victims. In this process, our methodology introduces the potential for workup bias. However, errors would occur only if a patient with a significant head injury exhibited none of our study criteria *and* was not selected for tomographic scanning. Such a case would represent an undetected false-negative event; the decision instrument would fail, and we would be unaware of the failure. Although such an event is theoretically possible, available studies indicate that essentially all significant head injury victims exhibit some symptomatology. As noted in our background discussion, there are no case reports describing significant intracranial injuries in an individual who does not exhibit at least one of our initial screening criteria. Furthermore, in our derivation study, we obtained follow-up evaluations on 1,266 patients who did not undergo computed tomography during their initial presentations. These evaluations revealed that a small minority of these patients ultimately received cranial imaging. However, none of these cases required hospitalization or neurosurgical intervention, and there were no cases of missed intracranial injuries or death among this cohort [65]. Thus, the potential for work-up bias is a theoretical possibility, but is of less practical concern. Furthermore, we will screen patient revisits and inpatient neurosurgical trauma admissions to identify patients who might produce such bias. Finally, as mentioned previously, we will obtain criteria evaluations and contact information for 368 consecutive blunt head trauma patients who present to the Ronald Reagan UCLA Medical Center and do not undergo emergent tomographic head imaging during their initial evaluation. We will contact these patients, or their family, three months after their enrollment to determine whether they were eventually diagnosed as having a significant intracranial injury or required hospitalization or neurosurgical intervention. The survey form used in these follow-up assessments is similar to the one used in the previous head injury study, and a copy of the survey form is presented in Appendix - D. Based on our previous experience, we estimate that we will be able to complete survey interviews on approximately 98% of the enrolled patients [65]. This process will effectively screen a large subset of patients who are not otherwise enrolled in the study, and will allow us to not only detect workup bias, but also estimate its magnitude. Thus, although we cannot completely eradicate the potential for measurement bias, our methodology makes it unlikely that it will be present without our knowledge.

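### The un-imaged follow-up cohort enrols exactly the 368 patients its 1.0% figure requires, with no allowance for the 2% loss the protocol itself expects; the shortfall is minor

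*Protocol*

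**What the plan says.** Section 4.3.3.1 states the requirement: "To verify the potential for work-up bias to with 1.0% requires a population of 368 head injury patients who do not receive CT imaging". The next sentence turns that requirement into the enrolment figure: "Thus we will enroll 368 consecutive patients in the work-up bias portion of the study". Section 4.3.9.1 repeats it as a count taken at the initial visit: "we will obtain criteria evaluations and contact information for 368 consecutive blunt head trauma patients".

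Section 4.3.3.1 also sets the rule for patients who are not reached within four weeks of the scheduled survey date: "Contact will be abandoned, and the patient deleted from the work-up bias evaluation". No replacement is mentioned.

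The expected completion appears twice. Section 4.3.3.1 reports the earlier experience: "we were able to obtain follow-up survey information on 98% of the patients who agreed to participate in the study". Section 4.3.9.1 carries it forward: "we estimate that we will be able to complete survey interviews on approximately 98% of the enrolled patients".

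**The concern.** The number required and the number enrolled are identical, yet the protocol removes unreached patients and expects to lose about 2% of them. These statements do not fit together: 368 enrolled at 98% completion does not give 368 patients with a known outcome.

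This cohort is the protocol's direct follow-up of patients who were never scanned, and so one of its checks for injuries that both the clinician and the decision instrument missed. At stake is whether the stated precision of that check is delivered under the protocol's own follow-up assumption.

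**Working it through.** **Inputs**
- Confidence level: section 3.2 sets α at 0.05, with α/2 = 0.025 in the tail of the exact limit.
- Target: lower limit P_L = 0.99, that is, an upper limit of 1.0% on the failure proportion (section 3.2).
- Events: no failures, X = N (section 3.2).
- Enrolled: 368 (sections 4.3.3.1 and 4.3.9.1).
- Completion: 98% (sections 4.3.3.1 and 4.3.9.1).

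Section 4.3.3.1 prints no formula for its own 1.0%. I assume it borrows the calculation of section 3.2, because that calculation returns the same 368.

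**Step 1: reproduce the 368.** With X = N the exact lower limit reduces to P_L = 0.025^(1/N). Setting P_L = 0.99:

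N = ln(0.025) / ln(0.99) = 367.04, rounded up to 368.

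A one-sided 5% tail would give ln(0.05) / ln(0.99) = 298.07, rounded up to 299. The printed figure therefore comes from the two-sided form, and it reproduces exactly.

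**Step 2: how much slack there is.** The upper limit with zero events among n patients is 1 − 0.025^(1/n).
- n = 368: 0.9974%
- n = 367: 1.0001%

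So 368 is the smallest number that works, with nothing to spare.

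**Step 3: apply the protocol's own completion rate.** 368 × 0.98 = 360.6, about 361 patients analysed. With zero events among 361:

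1 − 0.025^(1/361) = 1.017%.

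The excess over the limit at 368 is 1.017 − 0.997 = 0.02 percentage points.

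**Step 4: enrolment that would give 368 completed surveys.** 368 / 0.98 = 375.5, so 376 on average. Treating patients as independent, each with a 98% chance of completing:
- 376 enrolled: about a 66% chance of at least 368 completed surveys
- 380 enrolled: about a 96% chance

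**Step 5: sensitivity to lower completion.** As an illustration only, since the protocol gives no such figure: 90% completion leaves 331 patients and a limit of 1.11%; 80% leaves 294 and a limit of 1.25%.

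**The case against.** **The miss is invisible at the precision printed.** The protocol writes its target to one decimal, and 1.017% is 1.0% to one decimal. The limit still rounds to 1.0% with 350 completed surveys (1.048%), which is 350/368 = 95.1% completion. At 98% completion the chance of at least 350 is above 99.9%. This stands. A reader might infer that the target is almost never met, since the chance that all 368 complete is 0.98^368 = 0.06%, or that 1.0% could not be reported as achieved. The protocol does not support either inference. Both depend on treating 1.0001% at 367 patients as a failure, and section 2 itself describes the parallel requirement for sensitivity as only roughly 368 of 368.

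**The 1.0% may describe something else.** Section 4.3.3.1 measures work-up bias as the difference between sensitivity in the whole UCLA cohort and sensitivity in its imaged patients. Only patients needing neurosurgery enter that difference. If no un-imaged patient has an event, the estimated difference is zero whether 368 or 361 are followed. This also stands. A reader might infer that the shortfall weakens the protocol's measure of work-up bias whatever the 1.0% refers to. It does not: losing event-free patients leaves the sensitivity difference unchanged. The point holds only for the proportion of un-imaged patients with a missed neurosurgical injury.

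**Section 4.3.2.2 could mean 368 with outcomes.** It speaks of determining long-term outcome on a cohort of that size. This does not remove the problem. Sections 4.3.3.1 and 4.3.9.1 make 368 the number enrolled and apply the 98% to that number, so staff following the text would stop at 368 consents.

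**The survey is not the only safeguard.** Section 4.3.9.1 also plans to screen revisits and inpatient neurosurgical trauma admissions. That is correct, and it lowers the consequence further, but it does not reconcile the printed figures.

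**Conclusion.** The point holds as a small mismatch between a stated sample size and a stated precision. Under the protocol's own 98% completion, about 361 rather than 368 patients would contribute outcomes, and the zero-event exact limit would be about 1.02% rather than 0.997%.

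This rests on three assumptions: that the 1.0% is the exact two-sided 95% limit of section 3.2, that it applies to the proportion of un-imaged patients with a missed neurosurgical injury, and that no such injury is observed. The primary outcome, the instrument's sensitivity for injuries requiring neurosurgical intervention, is not affected. It is a correction of the lowest importance, worth making because it is almost free.

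**What to change.** Make one of two changes, in the same words in sections 4.3.3.1 and 4.3.9.1:

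1. Keep 368 enrolled, and state that about 361 completed surveys are expected, giving an upper 95% limit of about 1.02% if no events are seen. This costs only the rewording.
2. Define the 368 as completed three-month surveys and continue enrolment until they are reached. This takes about 376 enrolled on average; a fixed 380 gives about a 96% chance of 368. The cost is about 8 to 12 more consented patients (376 − 368 = 8; 380 − 368 = 12) at one site where section 4.3.2.2 already places research assistants in the emergency department continuously.

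Under either option, name the quantity the 1.0% bounds, so that it is not taken for a bound on the sensitivity difference.

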**4.3.4 - Patient Consent**

For most patients, this observational study collects information routinely obtained in the evaluation of blunt head trauma victims. This information should be documented in each patient’s medical record, although past experience has shown that physicians are not always meticulous in detailing their findings (this is part of the motivation for performing this study as opposed to a chart review). The study does not alter medical care, and therefore poses no risk to the welfare of patients or place them at any additional medical risk. In addition, the data will be indexed by study numbers assigned to each case at the time of enrollment, data will be recorded in such a manner that subjects will not be able to be identified, either directly or through identifiers linked to the subjects. These conditions comply with the terms for waiver of informed consent. The protocols in this project are compliant with new HIPAA regulations and have undergone IRB review and an appropriate waiver has been granted. Each participating institution will be expected to obtain an individual waiver of informed consent (this requirement is identical to the procedures in place for our previous study of *Selective Computed Head Tomography in Blunt Trauma* (PHS Grant No. R01 HS09699).

Study index numbers will be used to link radiographic results and the need for neurosurgical intervention to survey data. This can be accomplished in a manner identical to that used in our earlier studies using the following procedure. At the time a radiographic request is printed, an additional sheet is printed. The upper left corner of the sheet contains the patient’s medical record number, while the lower corner of the sheet contains the study index number. These sheets will be collected by site coordinators. By examining the upper left hand corner of each page, the coordinators will know which radiographic studies to retrieve. Once the radiographic study has been collected for a patient, the regional coordinators will place the lower right hand corner of the study sheet (containing the study index number) over the patient identifying information on the tomography report. The tomography report will then be photocopied with the study index number covering all identifying patient data, thus effectively redacting all identifying information from the tomography report. If the tomography report reveals an intracranial injury, the patient’s medical records for the associated visit will be reviewed, and the redacted tomography report will be modified by including a notation regarding the need, if any, for neurosurgical intervention. The redacted photocopies will then be forwarded to UCLA. Once the tomographic reports and need for neurosurgical intervention have been collected, redacted and photocopied, the sheets containing both patient medical record and study number will be cut in half to yield a one leaf with patient medical record number, and a separate leaf with the study index number. A mark will be placed on the leaf containing the patient medical record number of any patient requiring neurosurgical intervention. The study index numbers will be destroyed, while the medical record numbers will be retained for quality assurance reviews (see below). All sheets will be destroyed on study completion.

Informed consent will be obtained only on patients participating in the long-term follow-up survey at the Ronald Reagan UCLA Medical Center. Clinicians will assess the presence or absence of each study criterion for all blunt head injury victims presenting to this center. Cases selected for CT imaging will be entered into the study under the waiver of informed consent using the process described above. Patients who do not undergo tomographic imaging will be invited by their physicians to participate in the long-term outcome evaluation. Research assistants will provide information about the study and assist in obtaining informed consent from patients who express interest in participating in the study. Patients will not be enrolled in the follow-up study unless they (or their surrogates) provide informed consent.

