Injuries such as isolated linear or basilar skull fractures, solitary small cerebral contusions, localized subarachnoid hemorrhage less than 1 mm thick, thin subdural hematomas less than 4mm thick, isolated pneumocephaly, and closed depressed skull fractures that do not violate the inner table will not be considered to be significant injuries [63]. Coincidental or congenital abnormalities will also not be considered to be significant intracranial injuries. Chronic subdural hematomas, without evidence of acute change, will be considered to be coincidental injuries and will not be considered to be significant acute injuries. Chronic subdural hematomas that exhibit any recent change, or those that are of indeterminate age, will be considered to be acute significant injuries.

Research assistants, blind to classification by the decision rule, will review the medical records of patients with positive tomographic scans to determine whether or not the patient received neurosurgical intervention. The need for neurosurgical intervention is defined as any of the following within seven days of the initial injury [63]:

1 – Death due to intracranial injury.

2 – Intubation for management or support of head injury.

3 – Craniotomy, elevation of skull fracture or intracranial pressure monitoring.

Cases involving death or intubation will be reviewed by the physician liaison to determine, on the basis of their best clinical judgment, whether there was a causal relationship between the event and the patients intracranial injury. The liaisons will be instructed to consider these events as causally related to intracranial injury unless there is compelling evidence to the contrary. Patients will not be considered to have received neurosurgical intervention if their death is clearly due to causes unrelated to their head injury, or if they were intubated solely to expedite care.

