**4.3.7 - Data Analysis**

The primary outcome for the study is the point measure and associated 95% confidence interval for the sensitivity of the decision instrument in identifying patients who require neurosurgical intervention. Additional operator characteristics of interest for this population include the negative predictive value and specificity. Secondary outcomes include the sensitivity, negative predictive value and specificity of the instrument in detecting patients who harbor clinically significant intracranial injuries as described by the criteria defining positive CT imaging (see 4.3.5.1.2 - Injury Diagnosis above). A further secondary goal of the study is to determine and compare the operator characteristics of both the NEXUS head CT instrument, as well as both forms (“high risk” and “medium risk”) of the Canadian head CT instrument, among patients who meet the inclusion and exclusion characteristics for classification by the Canadian rules.

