**4.3.8.2 - Protection of Radiographic Data Integrity**

Preliminary diagnoses of "no injury" will be confirmed in two ways. First, quality assurance logs, which contain lists of significant radiological findings that were missed on preliminary reading, will be reviewed by the site liaisons during routine evaluations. Any revisions found on these surveys will be transmitted to UCLA where they will be incorporated into the study database. Second, the diagnoses of all blunt trauma patients admitted through the emergency department and discharged from the hospital during and up to three months after each study period will be searched and all intracranial injury cases identified. The charts of such patients will be reviewed to determine if the case was included in the study (using the patient number previously printed on the redacting forms), and if so, whether the case was classified as having an intracranial injury (based on whether the leaf was marked). The liaisons will notify core UCLA personnel of any cases of missed injury detected in this fashion. These cases will be reviewed by the site liaisons to determine, based on their best judgment, whether they involve protocol errors, and whether they represent a false-negative event (patient with a head injury, but “low-risk” according to the decision instrument). Site coordinators will notify core UCLA personnel of their findings. Reviews of the quality assurance logs and discharge diagnoses will be performed by the site liaisons on a bi-monthly basis.

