**5.2 - Adequacy of protection against risk**

The study poses no medical risk to patients, and the following actions will be taken to prevent any risk related to the confidentiality of medical records. Study index numbers will be used to link radiographic results and the need for neurosurgical intervention to survey data at all sites. At the time radiographic imaging is requested the patients medical record number will be recorded along with the study index number in an encoded file that will be available only to study research personnel. The information in this linkage file will be used to connect survey data with outcome data. The linkage files will be destroyed, after quality assurance reviews are complete and the study data is finalized.

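### Neurosurgical intervention is defined over seven days from injury, but outcome abstraction covers only the associated visit, and the protocol contradicts itself on keeping the link needed to classify cases found later

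*Protocol*

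**What the plan says.** Section 4.3.7 sets the endpoint: "The primary outcome for the study is the point measure and associated 95% confidence interval for the sensitivity of the decision instrument". The target condition is the need for neurosurgical intervention. Section 4.3.5.1.2 gives the window: "The need for neurosurgical intervention is defined as any of the following within seven days of the initial injury". The qualifying events are death, intubation or an operative procedure, including intracranial pressure monitoring.

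Two sections describe how the event is found. Section 4.3.5.1.2 says research assistants "will review the medical records of patients with positive tomographic scans to determine whether or not the patient received neurosurgical intervention" and sets no visit limit. Section 4.3.4 gives the working procedure and does set one: when the CT report shows an injury, it is the "medical records for the associated visit will be reviewed".

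Section 4.3.8.2 adds a back-up. Diagnoses of blunt trauma patients admitted via the emergency department and "discharged from the hospital during and up to three months after each study period will be searched". Charts are matched to enrolled patients by record number, and site liaisons judge whether a missed case was a false negative. This runs bi-monthly.

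On linkage, section 4.3.4 says: "The study index numbers will be destroyed, while the medical record numbers will be retained for quality assurance reviews". Section 5.2 says: "The linkage files will be destroyed, after quality assurance reviews are complete and the study data is finalized".

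**The concern.** The outcome window and the step that fills it do not match. A patient discharged from the associated visit who has an intervention on day 3 meets the definition in section 4.3.5.1.2, but the review in section 4.3.4 does not reach that event. Such a case can then be counted only through the back-up search. That search needs the survey record to tell a false negative from a true positive, and survey records are filed by study index number. Section 4.3.4 removes that number before quality review begins.

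The stakes are high because the design tolerates no misses. Section 2 requires 368 consecutive cases to be identified without a miss, and the stopping rule in section 4.3.10.3 (ten misses) uses the same count. Patients with none of the criteria are plausibly the ones most often sent home, so an incomplete count would tend to lose false negatives rather than true positives.

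**Working it through.** **Tracing one case through the sections.** Take an enrolled, imaged patient who is discharged and has an intervention at the same hospital on day 3.

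1. Definition (4.3.5.1.2): the event counts.
2. Abstraction (4.3.4): records are reviewed only if the CT report showed an injury, and only for the associated visit. The event is not found at this step.
3. Search (4.3.8.2): if the patient is admitted through the emergency department with an intracranial injury diagnosis, the chart is pulled and the record number matches a retained leaf. The leaf is unmarked, so the case is flagged.
4. Classification (4.3.8.2): the liaison must say whether the instrument labelled the patient low risk. Under 4.3.4 the index number has been destroyed. Under 5.2 an encoded file still links the two numbers.
5. Update: 4.3.8.2 sends the finding to the core team but does not say that it changes the seven-day outcome.

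The leaf mark is also inconsistent. Section 4.3.8.2 reads it as showing that an intracranial injury was recorded, but 4.3.4 marks it only for neurosurgical intervention. A patient with a recorded injury and no intervention therefore looks like a missed injury. This makes the flag ambiguous; it does not by itself lose cases.

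**Reproducing the plan's figure.** Inputs are α = 0.05 (used as α/2) and a target lower limit of 0.99 (section 3.2). With X = N, the exact lower limit is N / (N + F(α/2; 2, 2N)) = 0.025^(1/N).

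- ln(0.025) / ln(0.99) = 367.04, so N = 368.
- N = 367 gives 0.989999; N = 368 gives 0.990026.
- 368 / 0.012 = 30,667, stated in the plan as 31,000.

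Both figures reproduce.

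**Effect of uncounted false negatives.** Enrolment continues until 368 cases are counted (4.3.10.3), so an uncounted miss lies outside the 368. The numbers of uncounted misses below are assumptions.

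| Uncounted misses | True ratio | Sensitivity | Exact lower limit |
|---|---|---|---|
| 0 | 368/368 | 100% | 99.00% |
| 1 | 368/369 | 99.73% | 98.50% |
| 2 | 368/370 | 99.46% | 98.06% |
| 3 | 368/371 | 99.19% | 97.66% |
| 5 | 368/373 | 98.66% | 96.90% |

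With one miss, 555 cases would be needed to hold the lower limit at 99.0%, or 555 / 0.012 = 46,250 patients.

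**Direction.** Let s be the true sensitivity and c the fraction of false negatives captured, with every true positive captured. Apparent sensitivity is s / (s + (1 − s)c). For an assumed s = 0.99:

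| c (assumed) | Apparent sensitivity | Chance of no observed miss in 368 |
|---|---|---|
| 1.0 | 99.0% | 0.99^368 = 2.5% |
| 0.8 | 99.2% | 5.2% |
| 0.5 | 99.5% | 15.7% |

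If true positives and false negatives were lost at the same rate, there would be no bias. Upward bias needs greater loss among low-risk patients.

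**The case against.** A reader might infer that review stops at the associated visit, that every low-risk patient who returns is lost, and that sensitivity is therefore biased upward. The documents do not support this, for four reasons.

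- The visit limit appears in the consent section's redaction procedure, not in the outcome section. Section 4.3.5.1.2 collects the final reading of each head CT, includes in-patient studies, and reclassifies wrong initial diagnoses.
- The search in 4.3.8.2 reaches well past day 7 for same-hospital admissions and adjudicates possible false negatives. Section 4.3.9.1 also screens revisits and neurosurgical admissions, although its stated target is work-up bias.
- Section 5.2 keeps the linkage. Survey records also carry date of birth, date of injury, sex, race and institution (4.3.3), so matching might be possible without the index number, although no such procedure is described.
- Patients who could be lost may be few. Section 2 regards classically significant CT findings as grounds for admission, and section 4.3.9.1 treats injuries missed by CT as irrelevant to patient selection.

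These points defeat the claim of a demonstrated bias. They do not remove the conflict between 4.3.4 and 5.2, the absence of any statement of how seven-day status is obtained after early discharge, or the leaf-mark error. Section 4.3.9.1 does not cover CT-positive patients treated later, and it sits awkwardly with the reclassification rule in 4.3.5.1.2.

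**Conclusion.** The point holds as an internal inconsistency in how the primary outcome is ascertained. If 4.3.4 is followed as written, an early-discharged patient with an intervention by day 7 may go uncounted or unclassified. The back-up search narrows this gap for same-hospital admissions, provided the linkage survives as 5.2 says.

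The likely direction is upward for sensitivity. This rests on the assumption that low-risk patients are discharged more often, which is plausible but not quantified. The documents give no return rate, so the expected size of the bias cannot be computed. What can be said is that one uncounted false negative would reverse the validation result, since the lower limit for 368/369 is 98.5% against the required 99.0%. That sensitivity to a single case belongs to any zero-miss design and is no evidence that a case will be missed, but it justifies closing the gap.

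A separate gap remains. No follow-up is described for imaged patients who have an intervention, or die, outside the study hospital; the telephone survey covers only un-imaged patients at one site (4.3.2.2).

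**What to change.** 1. Amend section 4.3.4 so that outcome abstraction covers all study-hospital encounters through day 7 after injury, matching section 4.3.5.1.2.
2. Keep the link between index number and record number until the section 4.3.8.2 search is finished, as section 5.2 says, and reconcile the two sections.
3. State in section 4.3.8.2 that cases found by the search update the seven-day outcome and are classified from the survey record already on file. Correct the meaning of the leaf mark. Reconcile this with the position in section 4.3.9.1 on injuries missed by CT.
4. State in section 4.3.9 that interventions or deaths outside the study hospital among imaged patients are not captured.

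The cost is wording, slightly longer review of records the sites already hold and search, and later destruction of the linking sheets. No new patient contact is needed.
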